### **Pharmaceutical Information**

Storage, distribution, and usage of these materials in accordance with the protocol and any applicable laws and regulations.

Sarilumab (Kevzara®) pharmaceutical information according to authorized SmPC

Dose formulation:

Sarilumab 200mg: one single-dose pre-filled syringe containing 200mg sarilumab in 1.14 ml solution (175 mg/ml) added to 100mL 0.9% sodium chloride for a 1-hour intravenous infusion.  
Unit dose strength: 200mg

Sarilumab 400mg: two single-dose pre-filled syringe containing 200mg sarilumab in 1.14 ml solution (175 mg/ml) added to 100mL 0.9% sodium chloride for a 1-hour intravenous infusion.  
Unit dose strength: 400mg

*Route of administration:* intravenous

*Storage:* each box will be stored at the site at a temperature of 2°C to 8°C

*Packaging and labelling:* Study intervention will be provided in box by Sanofi. Each box will contain 2 prefilled syringes and will be labelled as required by local regulation.

*Dosing instructions:*

After removing the syringes from the refrigerator, they should be allowed to reach room temperature (<25°C).

Before starting the dilution procedure, the clinical center (Pharmacist or Nurse) will check that the syringes used for dilution do not contain any particles or discoloration. If any particulate matter, cloudiness or discoloration is detected, the syringe is to be quarantined, prohibited from use and reported to the Sponsor. IMP will not be removed.

Sarilumab prefilled syringe (1or 2 syringes for 200 mg or 400 mg dosage, respectively) will be diluted under aseptic conditions in 100 mL 0.9% Sodium Chloride solution bag. The infusion bag will be turned upside down at least three times to ensure a good mixing of the solutions.

The infusion will be administered within 30 minutes from the end of preparation (as no mixture stability is known). The product will be infused using a volumetric pump at the protocol-specific use and reported to the Sponsor. IMP will not be removed from the box until just before dosing in order to protect from light.

*Incompatibilities:* this medicinal product must not be mixed with other medicinal products.

*Manufacturer:* Sanofi-Aventis Groupe

### **Study drug preparation**

The local hospital pharmacist or nurse will prepare the treatment dose required for each patient. Individual treatment dose is prepared in the preparation area of the pharmacy, at a workstation free from any items not needed for this operation, and will be performed in aseptic conditions, as per local rules. Safety measures for preparation and handling include protective clothing, gloves, and safety cabinets.

### **Potential Risks**

#### Serious infections:

Patients should be closely monitored for the development of signs and symptoms of infection during treatment with Kevzara®. As there is a higher incidence of infections in the elderly population in general, caution should be used when treating the elderly.

#### Laboratory abnormalities:

The activity of sarilumab in reducing inflammation is associated with laboratory changes such as decrease in ANC and elevation in lipids.

Please refer to the SmPC for additional precautionary measures during sarilumab treatment (Appendix 5)

### **Administration**

Premedication is not required prior to the administration of sarilumab unless deemed medically necessary by the investigator.

Any participant experiencing an Infusion-related reaction (IRR) must receive appropriate medical treatment. When the participant's condition is stable, the infusion may be restarted at a slower rate. In general, upon restarting, the infusion rate must be decreased by half at the time the infusion was interrupted.

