## **3. BACKGROUND AND RATIONALE FOR THE STUDY**

### ***Drug Information***

Kevzara® (sarilumab) is a fully human IgG1 monoclonal antibody that binds specifically to both soluble and membrane-bound IL-6 receptors (sIL-6Rα and mIL-6Rα) and has been shown to inhibit IL-6-

mediated signaling through these receptors. IL-6 is a pleiotropic pro-inflammatory cytokine produced by a variety of cell types including T- and B-cells, lymphocytes, monocytes and fibroblasts. IL-6 has been shown to be involved in diverse physiological processes such as migration and activation of T-cells, induction of immunoglobulin secretion, initiation of hepatic acute phase protein synthesis, and stimulation of hematopoietic precursor cell proliferation and differentiation.

Kevzara® (sarilumab) is authorized in the European Union for the treatment of adult patients with moderately to severely active rheumatoid arthritis (RA) who have had an inadequate response or intolerance to one or more biologic or non-biologic disease-modifying anti-rheumatic drugs (DMARDs). The recommended dose is 200 mg once every 2 weeks given as a subcutaneous injection.

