**To evaluate safety of sarilumab as compared to SOC**

Safety through day 29

- Cumulative incidence of serious adverse events (SAEs)
- Cumulative incidence of Grade 3 and 4 adverse events (AEs).

Serious adverse events (SAEs).  
Grade 3 or 4 Adverse events (AEs).

|                                                                                                                                                   |                                                                                                                                    |
|---------------------------------------------------------------------------------------------------------------------------------------------------|------------------------------------------------------------------------------------------------------------------------------------|
| To evaluate differences in the effect of sarilumab on the serum levels of inflammatory cytokines in patients infected with COVID-19.       | Changes in serum level of CRP, IL-6, lymphocyte count, neutrophils count, d-dimer, LDH, ferritin, coagulation tests                |
| To evaluate differences in the proportion of patients showing more than >1 organ failure, e.g. cardiovascular, liver and kidney failure | Patients showing more than >1 organ failure through day 15                                                                         |
| To identify prognosis factors of sarilumab efficacy related to laboratory parameters or disease features                                   | Focused medical history, demographic characteristics, COVID-19 history, concomitant medication, and laboratory disease parameters. |

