### ***Study Intervention Compliance***

Participants will receive study intervention directly from the investigator or designee, under medical supervision. The date and time of each dose administered in the clinic will be recorded in the source documents and reported in the case report form (CRF). The dose of study intervention and study participant identification will be confirmed at the time of dosing by a member of the study site staff other than the person administering the study intervention.

Sarilumab will be intravenously administered to participants at the site.

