### ***Definitions***

Adverse Event is defined as any event that results in worsening of the health of the subject of the clinical trial, regardless of relationship to the experimental therapy. It can be any symptom, sign, illness or experience, including abnormal results of diagnostic procedures, that develops or worsens in severity during the course of the study.

Any medical condition that is present at the time that the subject is screened will be considered as baseline and not reported as an AE. However, if the severity of any pre- existing medical condition increases, it should be recorded as an AE.

Given the nature of severity of the underlying illness, subjects will have many symptoms and abnormalities in vitals and laboratory. Only Grade 3 and 4 AEs will be captured as AEs in this trial, according to the following classification:

- Mild (Grade 1): Events that are usually transient and may require only minimal or no treatment or therapeutic intervention and generally do not interfere with the subject's usual activities of daily living.
- Moderate (Grade 2): Events that are usually alleviated with additional specific therapeutic intervention. The event interferes with usual activities of daily living, causing discomfort but poses no significant or permanent risk of harm to the research subject.
- Severe (Grade 3): Events interrupt usual activities of daily living, or significantly affects clinical status, or may require intensive therapeutic intervention. Severe events are usually incapacitating.
- Very severe (Grade 4): Events that are potentially life threatening.

Serious Adverse Event are defined as any AE (or adverse reaction) that in the view of either the investigator or the sponsor, it results in any of the following outcomes:

- Fatal
- Life-threatening\*
- Requires or prolongs hospital stay
- Results in persistent or significant disability or incapacity
- A congenital anomaly or birth defect

The concept "life-threatening" means that in the opinion of the investigator, the patient is in real danger of death in the AE situation; it does not mean that the AE could have caused death if it would have been more intense.

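### The protocol contradicts itself on which adverse events are captured; if the Grade 3-4 rule in section 9 is followed, non-serious infusion-related reactions below Grade 3 can go unrecorded

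*Protocol*

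**What the plan says.** **Statements that limit capture by grade.** Section 9 (Definitions) says: "Only Grade 3 and 4 AEs will be captured as AEs in this trial". The reason given is that these patients are severely ill and will have many symptoms and abnormal findings anyway. Table 1 in section 4 names two safety measures, the cumulative incidence of serious adverse events and that of Grade 3 and 4 events.

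**Statements with no grade limit.** Five places cover adverse events of any grade:
- the synopsis, which lists safety and tolerability among the secondary endpoints;
- section 8, secondary endpoint 11, which counts adverse events, serious events and laboratory abnormalities;
- section 8, Calendar of Evaluation of Trial Variables, under which every adverse event is collected for up to 28 days;
- the opening of section 9, which puts every adverse event in the CRF with an NCI-CTC v5.0 grade;
- section 9, Registry of AE, which repeats that all are documented in the CRF.

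**Infusion reactions.** Section 3 (Drug Information) gives the product's recommended use as subcutaneous: "The recommended dose is 200 mg once every 2 weeks given as a subcutaneous injection". In this trial it is given as a one-hour intravenous infusion. Section 7 (Administration) requires that a participant with an infusion-related reaction be treated, and adds that when the participant's "condition is stable, the infusion may be restarted at a slower rate". It assigns no grade to such a reaction. No endpoint names infusion-related reactions.

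**Dose records.** Section 7 (Study Intervention Compliance) says: "The date and time of each dose administered in the clinic will be recorded". It also has a second staff member confirm the dose and the participant's identity at dosing. It does not mention interruption or completion of the infusion.

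**The concern.** The Definitions section describes Grade 2 as "Events that are usually alleviated with additional specific therapeutic intervention". An infusion reaction that is treated, settles and lets the infusion restart can fit that description. If it is not serious, it falls outside both the capture rule in Definitions and the two measures in Table 1.

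Infusion reactions are a foreseeable harm of giving the drug by a route other than its recommended one, and the protocol itself plans for them. The reason offered for the grade limit is background illness. That reason applies poorly to an acute reaction during a supervised one-hour infusion, which is comparatively easy to tell apart from COVID-19 symptoms.

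At stake is part of the safety and tolerability objective. Sites that apply the Definitions rule would not record these reactions and sites that apply the Registry of AE rule would. A pooled count would then mix two rules and have no clear denominator. Data on a single infusion that are not collected at the time may not be recoverable later.

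**Working it through.** **1. Inputs.** The number given sarilumab is taken as the planned experimental arm of 100 (section 10, Sample size estimation). That figure reproduces. With 25% against 10%, two-sided 5% significance and 80% power, the mean proportion is 0.175 and

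n = [1.960 × √(2 × 0.175 × 0.825) + 0.842 × √(0.25 × 0.75 + 0.10 × 0.90)]² / 0.15² = (1.053 + 0.443)² / 0.0225 ≈ 99.5, so 100 per arm (power 80.2%).

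This point does not affect the sample size. The documents give no infusion-reaction rate, so a range is assumed.

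**2. The same event under each rule.** Take a non-serious infusion reaction that is treated and followed by a restart:
- Section 9, Definitions: captured only if Grade 3 or 4, so not captured at Grade 2.
- Section 4, Table 1: not counted in either safety measure.
- Synopsis, endpoint 11, Calendar of Evaluation, opening of section 9, Registry of AE: recorded and counted, but only within total adverse events.

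Take instead a reaction that is serious or reaches Grade 3: it is captured under every one of these statements.

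**3. Can the two sets be read as consistent?** One reading is that Definitions fixes what counts as an adverse event in this trial, and that the other sections then mean all events meeting that definition. On that reading milder reactions are lost. The other reading gives the ungraded statements their plain sense, and the Definitions sentence is then wrong. The protocol does not choose. It does make an exception to the limit for laboratory abnormalities that the investigator judges clinically significant (section 9, Clinically Significant Laboratory Abnormalities). It makes none for infusion reactions.

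**4. Size if the Definitions rule is followed everywhere.** Let p be the true rate of non-serious reactions below Grade 3. The expected number missed is 100 × p, and the chance that at least one occurs is 1 − (1 − p)^100.
- p = 1%: 1 missed; chance of at least one 63%.
- p = 3%: 3 missed; 95%.
- p = 5%: 5 missed; 99.4%.
- p = 10%: 10 missed; over 99.9%.

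**5. If sites differ.** If half of the patients are at sites that apply the Definitions rule, the expected number missed is 100 × p × 0.5, that is 0.5, 1.5, 2.5 or 5.

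**6. Rescue infusions.** At the sizing rate of 25%, at most 0.25 × 100 = 25 controls would reach the primary endpoint and so possibly a rescue infusion. At the same rates that adds at most 25 × p = 0.25, 0.75, 1.25 or 2.5 reactions. This is an upper limit, because the 25% includes ICU admission and death and not every progressing patient will be rescued.

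**The case against.** The strongest reply is that most of the protocol does cover these reactions. Endpoint 11 stands in the section that formally lists the study outcomes, has no grade limit, and has a time frame that includes the infusion day. The Calendar of Evaluation, the opening of section 9 and Registry of AE agree with it. A reader who looks only at Table 1 might infer that the safety endpoints count nothing below Grade 3. The documents do not support that, and this part of the reply stands. What remains is the contradiction, and the loss that follows if Definitions prevails.

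Four further inferences also go beyond the documents:
- **That every treated and restarted reaction is Grade 2.** Section 7 assigns no grade. The Grade 3 wording includes an event that "significantly affects clinical status, or may require intensive therapeutic intervention", and a reaction that stops the infusion could meet it. Some could also be handled as important medical events. Grading is by CTCAE v5.0, whose text is not in the protocol.
- **That a partly infused patient will look fully dosed, or that the per-protocol set cannot identify incomplete doses.** This argues from silence. The eCRF is not shown, the dose is checked by a second person, and major deviations are assessed at data review before lock.
- **That a report of no reactions in 100 patients would mislead.** The exact upper bounds for 0/100 are 1 − 0.05^(1/100) = 2.95% (one-sided 95%) and 1 − 0.025^(1/100) = 3.62% (two-sided 95%). For a table labelled Grade 3-4 these are correct bounds on Grade 3-4 reactions. They mislead only if read as covering any grade.
- **That the intravenous route is itself under test.** There is no subcutaneous arm; the comparison is sarilumab plus standard of care against standard of care.

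It can also be said that dedicated infusion fields are eCRF detail. That is fair for the layout of the form, but which grades are captured is fixed in the protocol text, and fixed in two incompatible ways.

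**Conclusion.** The concern holds as a contradiction over adverse event capture with one specific consequence. Section 9 (Definitions) and Table 1 conflict with endpoint 11, the synopsis, the Calendar of Evaluation, the opening of section 9 and Registry of AE. If the Definitions rule is followed, non-serious infusion-related reactions below Grade 3 can go unrecorded.

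The size is about 1, 3, 5 or 10 missed reactions among 100 treated patients at assumed rates of 1%, 3%, 5% or 10%, with at most a few more from rescue infusions. This assumes that 100 patients receive sarilumab, that the reactions counted are below Grade 3 and not serious, and that all sites apply the Definitions rule. The rate is an assumption throughout.

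The primary endpoint and the sample size are unaffected. This is a cheap improvement to the safety objective and does not show that the safety plan as a whole fails.

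**What to change.** 1. Reconcile section 9 (Definitions) and Table 1 with the synopsis, endpoint 11, the Calendar of Evaluation, the opening of section 9 and Registry of AE, so that one rule says which grades are recorded and which are summarised.
2. Whatever general rule is kept, state that infusion-related reactions of any grade are exempt from the Grade 3-4 limit, and add them to the Table 1 safety measures.
3. For every sarilumab infusion, randomised or rescue, record any such reaction and its grade, and whether the infusion was interrupted or completed.
4. Report the proportion of patients with a reaction, with an exact (Clopper-Pearson) 95% confidence interval, separately for randomised and rescue infusions.

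The cost is a few fields completed by staff already present at the infusion, and one extra table. The downside is slightly more data entry. How reactions are managed does not change.

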### **Packaging and Labeling**

All study drugs will be administered as open label. No blinding methods will be used in this trial.

Experimental drugs will be supplied to pharmacies packaged and labeled according to the standard requirements for clinical trials. Sarilumab will be labelled with the study protocol code, batch number, content, expiry date, storage conditions, investigator and sponsor name. The study medication will be labelled in accordance with annex 13 of the European Good Manufacturing

## Practices.

Each infusion bag will be clearly marked with the following information:

- Investigational site study code / Sponsor study code:
- Product code:
- Route of administration: For IV administration
- Patient number:
- Dose: 200 mg or 400mg unit
- For clinical trial use only

## **Handling and Storage**

All study treatment supplies must be stored in accordance with the manufacturer's instructions and package labeling. Until dispensed to the participants, the study treatment will be stored in a securely locked area, accessible to authorized personnel only. All study interventions must be stored in a secure, environmentally controlled, and monitored (manual or automated) area in accordance with the labeled storage conditions with access limited to the investigator and authorized site staff.

Upon receipt, sarilumab will be placed into a refrigerator and stored between +2°C and +8°C.

The investigator or designee must confirm appropriate temperature conditions have been maintained during transit for all study intervention received and any discrepancies are reported and resolved before use of the study intervention.

If a temperature excursion occurs:

- The affected products will be placed in quarantine immediately with a clear sign of "quarantined" and clearly separated from the rest of the supplies. In addition, the affected products will be stored under proper conditions as per storage requirements.
- The Site Monitor will be informed about the temperature excursion within the same business day.

## **Dispensing**

Only participants enrolled in the study may receive study intervention and only authorized site staff may supply or administer study intervention. The investigator agrees that study drug will be dispensed by the investigator or sub-investigator(s) named on the Investigator Agreement or their qualified designees. The investigator, sub-investigators, or qualified designees also agree that the study drug(s) will be dispensed only to study subjects who have provided written informed consent (or oral consent where appropriate) and have met all entry.

## **Accountability**

The investigator or the institution, is responsible for study intervention accountability, reconciliation, and record maintenance (i.e., receipt, reconciliation, and final disposition records).

An accurate accountability record of products received, dispensed, discarded and returned or

destroyed by the pharmacy at the investigator site will be maintained on pharmacy file.

### ***Study Intervention Compliance***

Participants will receive study intervention directly from the investigator or designee, under medical supervision. The date and time of each dose administered in the clinic will be recorded in the source documents and reported in the case report form (CRF). The dose of study intervention and study participant identification will be confirmed at the time of dosing by a member of the study site staff other than the person administering the study intervention.

Sarilumab will be intravenously administered to participants at the site.

### ***Disposal and Destruction***

Precaution will be taken to avoid direct contact with the study interventions. In the case of unintentional occupational exposure notify the Medical Monitor.

Sarilumab is for single use only. Any waste material should be disposed of in accordance with local requirements. Unused medicinal product can be used as rescue medication of the study participants. Non-used medication will be returned to Sanofi or kept at local pharmacy for regular use upon Sponsor agreement. Medication will not be destroyed.

### ***Permitted Concomitant Therapy***

Participants should receive full supportive care during the study, as well as treatment with antibiotics and analgesics, as appropriate. All concomitant therapies will be permitted. No restriction is established regarding concomitant treatment.

Only clinical relevant concomitant treatment related to COVID-19 will be recorded for the purposes of the trial. The list of concomitant medications will be assessed from 8 weeks prior to enrolment to end of study.

### ***Prohibited Concomitant Therapies***

The following medications are prohibited while receiving protocol therapy:

- Concomitant administration of tocilizumab.
- Any investigational agents other than sarilumab.
- Concurrent use of live vaccines.
- Other immunomodulators or immunosuppressant medications.

### ***Withdrawal from randomized treatment or from the study***

Patients are free to withdraw from participation in the study at any time. Patients are listed as having withdrawn consent only when they no longer wish to participate in the study and no longer authorize the Investigators to make efforts to continue to obtain their outcome data. Every effort should be made to encourage patients to remain in the study for the duration of their planned outcome assessments. In the case of a patients becoming lost to follow-up, attempts to contact the patient be made and documented in the patient's medical records.

Treatment discontinuation is not foreseen given that sarilumab therapy will be given as a single dose administration during the initial randomized phase. For patients progressing to severe

respiratory failure, the study foresees the possibility to administer sarilumab as rescue therapy under certain conditions. Patients may decide not to receive sarilumab in this second phase of the study without any justification, but efforts should be made by investigators to collect reasons behind and to continue to obtain their outcome data. Investigators may choose to discontinue treatment in this second phase due to severe toxicity to sarilumab during prior administration or due to any other medical reason for which treatment with sarilumab is not considered a suitable choice for the patient.

